### Sample size

The study will enroll a total of 1,395 patients, accounting for a 5% dropout rate. The sample size calculation is based on achieving a precise estimate of the expected interobserver agreement measured by Cohen’s Kappa coefficient, assumed to be 0.80, with a desired precision of ± 0.11 and a confidence interval of 95%. Additionally, assuming a 10% incidence of difficult Tracheal Intubation (TI), this sample size will ensure adequate representation for meaningful secondary analyses.^6^ Patient recruitment is anticipated to take between 12 and 18 months, starting in September 2024.

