## Introduction

Tracheal Intubation (TI) remains a cornerstone of airway management in both anesthesia and critical care, despite its routine use.^1^^,^^2^ Difficult intubation occurs in approximately 5%–8% of cases, while failed TI is reported in 0.05%–0.35% of cases.^3^ Recent data indicate a decline in these rates ‒ 1.6 and 0.06 per 1,000 cases, respectively ‒ primarily due to advances such as Videolaryngoscopy (VL).^4^ Nonetheless, airway management complications remain a significant cause of morbidity and mortality.^5^^,^^6^

Direct Laryngoscopy (DL) has traditionally been the gold standard for visualizing the glottis and guiding tracheal tube placement.^7^ The advent of VL in 2001 marked a significant milestone, reducing rates of difficult and failed airways.^8^ Consequently, several national and international societies ‒ including the American Society of Anesthesiologists (ASA), the Canadian Airway Focus Group (CAFG), and the Spanish Society of Anesthesiology and Resuscitation (SEDAR) ‒ now recommend VL as a first-line technique for TI due to its ability to reduce complications and improve clinical outcomes.^9^, ^10^, ^11^

Traditional classification tools ‒ such as the Cormack-Lehane scale, its modification by Yentis and Cook, and the Percentage of Glottic Opening (POGO) ‒ remain the most commonly used methods for assessing intubation difficulty.^7^^,^^12^, ^13^, ^14^ However, these tools were originally developed for direct laryngoscopy and may not fully capture the specific challenges associated with VL.^15^ For example, excellent glottic visualization (e.g., 100% POGO) during VL does not always guarantee procedural success^16^^,^^17^ due to difficulties in maneuvering and inserting the tube through the glottis.^18^, ^19^, ^20^ Although alternative scales have been proposed to overcome these limitations, none have gained widespread acceptance.^16^^,^^21^

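### The sample of 1,395 does not follow from a precision of ±0.11 for kappa; it matches a total 95% CI width of 0.11, that is ±0.055

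*Protocol article*

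**What the plan says.** The Sample size section of the protocol article gives the enrolment target in one sentence: "The study will enroll a total of 1,395 patients, accounting for a 5% dropout rate". The next sentence says that the target rests on a precise estimate of agreement, with kappa "assumed to be 0.80, with a desired precision of ± 0.11 and a confidence interval of 95" percent. A third sentence, introduced as an additional consideration and tied to the secondary analyses, continues "assuming a 10% incidence of difficult Tracheal Intubation (TI").

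The Statistical methods section names Cohen's kappa between the intubating anesthesiologist and one independent observer, so there are two raters per intubation. The Sample size section gives no formula, no number of rating categories and no marginal frequencies for the kappa calculation. Nowhere does the article describe 0.11 as a total interval width.

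**The concern.** The symbol ± denotes a half-width, so the plan as printed aims for an interval of about 0.69 to 0.91 around kappa 0.80. A sample of almost 1,400 pairs is large for that aim, which suggests that either the sample size or the precision is misstated.

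This is the only quantitative justification for the primary outcome. A reader who takes ±0.11 at face value will think that the study recruits about four times as many patients as its aim needs. The same reader would misjudge what a shortfall in recruitment does to the intended precision, because the design appears to have aimed for an interval half as wide, about 0.745 to 0.855.

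**Working it through.** **Inputs from the Sample size section:** kappa k = 0.80; precision 0.11; 95% confidence (z = 1.96); dropout 5%; incidence of difficult intubation 10%.

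**Assumptions:** a two-category rating, and the 10% used as its marginal prevalence p. The article states neither.

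**Formula.** For two raters and a binary rating, the large-sample variance of kappa is V/n, with

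V = (1 − k)[(1 − k)(1 − 2k) + k(2 − k) / (2p(1 − p))].

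For k = 0.80 and p = 0.10:

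V = 0.20 × [0.20 × (−0.60) + 0.96/0.18] = 0.20 × (−0.12 + 5.3333) = 1.0427.

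For a half-width h, n = z²V/h², rounded up. Enrolment is n/0.95, rounded up.

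**Step 1: the plan's figure as printed, h = 0.11.**
n = 1.0427 × (1.96/0.11)² = 331.02, so 332 pairs; 332/0.95 = 349.5, so 350 enrolled. The stated 1,395 is not reproduced.

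**Step 2: 0.11 as the total width, h = 0.055.**
n = 1.0427 × (1.96/0.055)² = 1,324.09, so 1,325 pairs; 1,325/0.95 = 1,394.7, so 1,395 enrolled. This is an exact match, dropout included.

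**Step 3: can another method rescue ±0.11 at 10% prevalence?**

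| Variant at ±0.11 | Evaluable | Enrolled |
|---|---|---|
| General Fleiss-Cohen-Everitt variance | 332 | 350 |
| Simple variance, po(1 − po)/(1 − pe)² | 341 | 359 |
| Goodness-of-fit interval, lower limit 0.69 | 453 | about 476 |
| One-sided z | 234 | 247 |
| Three categories at 89%, 10% and 1% (illustrative) | 301 | 317 |

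If kappa is left free, the least favourable value (about 0.37) needs about 703 pairs. None of these comes near 1,395.

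**Step 4: can another prevalence rescue ±0.11?** With the Step 1 formula:

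| Prevalence | Evaluable | Enrolled |
|---|---|---|
| 5% | 635 | 669 |
| 8% | 407 | 429 |
| 10% | 332 | 350 |
| 20% | 183 | 193 |
| 50% | 115 | 122 |

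To reach 1,325 pairs at ±0.11 the prevalence would have to be about 2.3%, a figure that the article does not give.

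**Step 5: expected half-width with 1,325 evaluable pairs and kappa 0.80.** ±0.055 at 10%, ±0.061 at 8%, ±0.076 at 5%.

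**The case against.** The strongest reply is that the reconstruction supplies inputs that the article does not. The 10% is attached to the secondary analyses and not to kappa, and the number of categories is not stated. A prevalence near 2.3% would give 1,395 at ±0.11, so it cannot be said that the total-width reading is the only possible one. This stands, and it limits the conclusion about where the error came from. It does not restore the printed figure, because no prevalence from 5% to 50% brings ±0.11 near 1,395.

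The second reply is that the discrepancy does no harm to the study. This also stands. At 10% prevalence 1,395 gives about four times the pairs that ±0.11 needs. The final interval will come from the data, and no rule in the article uses ±0.11 as a test of adequacy or as a reason to stop recruiting.

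Three stronger readings are tempting and are not supported:

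- A reader might infer that the sample was wrongly planned for a binary item when the primary outcome is the whole VCI score. The article never says that the calculation was binary; that is an assumption of this check.
- A reader might set the 10% against the Introduction, where "Difficult intubation occurs in approximately 5%–8% of cases", and call it wrong. Those are background figures. The study defines its own difficult category by the need for adjuncts, and the Introduction does not say that its figures use that definition. At 5% and 8% the expected half-width is still inside ±0.11.
- A reader might carry over the more recent rates, "1.6 and 0.06 per 1,000 cases, respectively", and conclude that almost no difficult cases will be seen. The same difference in definition rules this out.

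**Conclusion.** The stated precision is wrong as written. Under a two-rater, two-category kappa of 0.80 with a 10% marginal, ±0.11 corresponds to 350 enrolled patients, and 1,395 corresponds to ±0.055. The exact match, reached with figures printed in the same section and including the dropout allowance, makes it most probable that the total interval width was printed after a ± sign. That explanation rests on taking the 10% as the kappa marginal of a binary rating, and the sponsor needs to confirm it.

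This is a correction to a stated planning figure. It is not evidence that the study is too small or that its primary analysis is compromised.

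**What to change.** The sponsor should first check the inputs of its own sample size calculation. If they are confirmed, the Sample size section should:

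1. state the precision as a total 95% CI width of 0.11 (±0.055) for kappa 0.80;
2. name the rating and the marginal prevalence that were used, and the formula or software;
3. give 1,325 evaluable pairs and 1,395 enrolled after 5% dropout, with the enrolment target unchanged.

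Optionally, add the expected half-width if difficult intubation is less frequent than assumed: about ±0.061 at 8% and ±0.076 at 5%. If the check shows other inputs, those should be printed so that 1,395 can be reproduced. The cost is a sentence or two of wording, with no extra patients and no change to the analysis.

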### Ethics and dissemination

#### Ethical approval of research

The VCISpain study complies with the principles outlined in the Declaration of Helsinki and the GCP Guidelines. Ethical approval has been granted by the Research Ethics Committee of the University of Navarra (session of September 5, 2024, reference 2022.079 mod1). The study was registered at ClinicalTrials.gov (NCT06537531), ensuring adherence to transparency and high ethical standards. Oversight of ethical compliance will be managed by the principal investigator and coordinators in collaboration with the University of Navarra (UNAV).

#### Confidentiality

To uphold participant confidentiality, all original records will be securely stored at the participating centers for five years after the study’s completion. The electronic database will be thoroughly cleaned, anonymized, and retained for this period; this approach guarantees compliance with data protection regulations and ensures the safeguarding of participant information.

## Discussion

Airway management is a cornerstone of anesthetic practice; however, difficult tracheal intubation remains a significant concern, as highlighted by a recent audit in the United Kingdom.^6^ The introduction of VL has transformed airway management by providing superior glottic visualization, increasing first-attempt success rates, and reducing complications associated with multiple intubation attempts, such as hypoxemia, laryngeal trauma, and esophageal intubation.^25^ Nevertheless, the widespread adoption of VL continues to be limited by challenges related to training,^26^ financial constraints, and, notably, the lack of a standardized classification tool for documenting and communicating VL findings.^23^

The VCISpain study aims to bridge this gap by validating the VCI scale. This tool is designed to establish a standardized and reproducible language for airway management with videolaryngoscopy, addressing the limitations of traditional classification systems such as the Cormack-Lehane scale. Unlike these conventional tools, the VCI scale captures the unique features of videolaryngoscopy, particularly the “you see, and you fail” phenomenon, in which excellent glottic visualization does not necessarily ensure successful intubation.^17^ By standardizing communication, the VCI scale can enhance planning for future airway treatments, ultimately promoting patient safety.

The VCI scale integrates three key components: blade type (Macintosh or hyperangulated), the POGO score, and the ease or difficulty of the intubation procedure. This tool not only enhances documentation but also facilitates communication among clinicians, while supporting training and standardization in advanced airway management.

A previous study demonstrated the accuracy and reproducibility of the VCI scale in describing VL intubations.^22^ With its multicenter design ‒ encompassing 35 Spanish hospitals and anesthesiologists with varying levels of experience ‒ the VCISpain study provides a representative reflection of real-world clinical practice in Spain. Moreover, standardized training on the study protocol and the use of the VCI scale will help ensure the quality and reproducibility of the collected data.

This study offers several strengths, including the pioneering evaluation of the VCI scale in a multicenter setting, providing robust data on its reproducibility and clinical utility. Its pragmatic design minimizes interference with standard care, enhancing its relevance to everyday clinical practice.

Despite certain limitations ‒ such as heterogeneity among participating centers and variability in videolaryngoscope models and operator experience ‒ these factors may, in fact, increase the external validity of the findings by reflecting real-world clinical diversity.

One notable limitation is the absence of a direct comparison with existing classification systems, which prevents definitive conclusions regarding the superiority of the VCI scale over other tools.^16^ However, although not directly compared in this study, the VCI scale may offer advantages by integrating blade type, glottic view, and ease of intubation into a single, videolaryngoscopy-specific tool. It enhances clinical communication and documentation, not by replacing traditional scales, but by complementing them with context-specific information relevant to modern airway management.

The VCISpain study represents a significant step toward standardizing the communication of information related to videolaryngoscopy-guided tracheal intubation.^27^ Validation of the VCI scale has the potential to establish a new benchmark for both national and international clinical practice, informing future airway management guidelines. Integrating the VCI scale into routine care may improve patient safety, foster interdisciplinary collaboration, and support continuous professional development.

## Conclusion

In conclusion, VCISpain represents a cultural shift in airway management through the use of videolaryngoscopy. By establishing a common language, it has the potential to promote interprofessional collaboration, support clinical education, and improve airway management planning. It also paves the way for future research in anesthesiology.

Beyond its practical applications, the VCI scale reflects a broader commitment to continuous improvement and innovation in patient care, emphasizing safety and effective clinical communication as cornerstones of modern anesthetic practice.
